### 7.2.2 SLE DISEASE ACTIVITY INDEX (SLEDAI-2K)

The SLE Disease Activity Index 2000 (SLEDAI-2K) is an established, validated SLE activity index. It is based on the presence of 24 characteristics in 9 organ systems and measures disease activity in SLE patients over the last 30 days; the index is weighted according to the respective features. The features are scored by the evaluating clinician if they were present within the last 30 days, with more severe features having higher values, and then simply added together to determine the SLEDAI 2K total, which ranges from 0 to 105 [12, 65-67]. The baseline measurement for SLEDAI-2K is defined as the closest measurement taken before baseline administration of the study drug. SLEDAI improvement is defined as a reduction in the overall SLEDAI-2K score from baseline. No worsening of the SLEDAI 2K total score from baseline is defined as a change  $\leq 0$  in the SLEDAI 2K score.

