### 7.3.3 SLE RESPONDER INDEX (SRI-4)

The SRI-4 response is defined as  $\geq 4$ -point reduction from baseline in SLEDAI-2K score, no new BILAG A and no more than 1 new BILAG B domain score, and no worsening from baseline in the PGA ( $< 10\%$  worsening from baseline) [65]. For the endpoint analysis in this study, SRI-4 composite response is the proportion of subjects who achieve a SLEDAI-2K SRI-4 response at Week 3, 5, 7, 9, 12, 16, 20, 24, 28, 32, 36 of the core study period, and at Week 42, 48, 54, 60, 66, 72, 78 and 84 of the LTE observational period.

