### 7.6.3 CLINICAL LABORATORY TESTS

The following laboratory tests will be performed by the local laboratory (unless otherwise specified) and according to the flow chart in chapter 7.1.1:

- Hematology Panel
  - Hemoglobin
  - Hematocrit
  - White blood cell (WBC) count with differential (basophils, eosinophils, lymphocytes, monocytes, neutrophils)
  - Platelet count
- Serology Laboratory
  - Anti-dsDNA antibodies
  - Immunoglobulin isotype profile (IgG, IgM, IgA levels)
  - Serum complement factors C3 and C4
  - Antinuclear antibodies (ANA)
  - Antiphospholipid antibodies, including anti-cardiolipin, anti- $\beta 2$ -glycoprotein and anti-phosphatidylserine antibodies (repeated measurements only if present at baseline)
  - Extractable nuclear antibodies (ENA), including anti-Ro/SSA, anti-La/SSB, anti-ribonucleoprotein (anti-RNP), anti-U1RNP, anti-Sm (repeated measurements only if present at baseline)
  - rheumatoid factor, and anti-cyclic citrullinated peptide (repeated measurements only if present at baseline)
  - anti-Tetanus-Toxoid (TT), anti-Diphtheria and anti-Measles antibody titers
- Serum Chemistry Panel
  - Sodium
  - Potassium
  - C-reactive protein
  - Total protein
  - Creatinine
  - Creatinine kinase
  - Alanine aminotransferase
  - Aspartate aminotransferase
  - NT-Pro BNP
  - total bilirubin, and if total bilirubin is abnormally elevated, then direct bilirubin, and indirect bilirubin
- -Blood bank

- Antiglobulin (Coombs) test at baseline (compatibility testing/crossmatch), and repeated only if pathologic at baseline
- Coagulation Labs
  - Partial Thromboplastin Time
  - Prothrombin Time
  - International Normalized Ratio (INR)
- Urine Analyses – Fresh spot urine
  - Urine dipstick
  - Urine sediment evaluation
  - Urinary protein/creatinine ratio
- Urine pregnancy testing for women of childbearing potential only or serum pregnancy test (at the discretion of the Investigator)
- Viral serology (HBsAg, anti-HBs, and HCV antibody)
- QuantiFERON® -Tuberculosis test

The investigator must review the laboratory results in a timely manner, document, date and sign the results. All clinically relevant changes in laboratory results that occur during the study must be documented as adverse events in the CRF. The laboratory reports must be filed together with the other source documents.

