## B) SLE ACTIVITY SCORES (SLEDAI-2K, BILAG)

### SLEDAI-2K (SLE Disease Activity Index)

Mark, if the descriptor is present at the time of visit or the preceeding 10 days

| Symptom                       | Definition                                                                                                                                                                                                                                      | Points |                          |
|-------------------------------|-------------------------------------------------------------------------------------------------------------------------------------------------------------------------------------------------------------------------------------------------|--------|--------------------------|
| Seizure                | Recent onset (last 10 days). Exclude metabolic, infection or drug cause, or seizure due to past irreversible CNS damage.                                                                                                                        | 8      |  |
| Psychosis              | Altered ability to function in normal activity due to disturbance in perception of reality. Include hallucinations, incoherence, marked loose association, bizarre or disorganized behaviour.                                                   | 8      |  |
| Organic brain syndrome | Altered mental function with impaired orientation, memory or other intellectual function, with rapid onset. Include clouding of consciousness plus two of following: perceptual disturbance, incoherent speech, insomnia or daytime drowsiness. | 8      |  |
| Visual disturbance     | Retinal changes and eye changes. Include cytooid bodies, retinal hemorrhage, serous exudate in the choroid, optic neuritis, scleritis or episcleritis. Exclude hypertension, infection, drugs.                                                  | 8      |  |
| Cranial nerve disorder | New onset of sensory or motor neuropathy involving cranial nerves. Include vertigo due to lupus.                                                                                                                                                | 8      |  |

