|------------------------------|------------------------------------------------------------------------------------------------------------------------|---|--------------------------|
| Proteinuria           | New onset or recent increase of more than 0,5mg/24hours.                                                               | 4 |  |
| Pyuria                | > 5 white blood cells/high field. Exclude infection.                                                                   | 4 |  |
| Rash                  | Ongoing inflammatory lupus rash.                                                                                       | 2 |  |
| Alopecia              | Ongoing abnormal, patchy or diffuse loss of hair.                                                                      | 2 |  |
| Mucosal ulcers        | Ongoing oral or nasal ulcerations.                                                                                     | 2 |  |
| Pleurisy              | Pleuritic chest pain with pleural rub or effusion, or pleural thickening.                                              | 2 |  |
| Pericarditis          | Pericardial pain with at least 1 of the following: rub, effusion, or electrocardiogram or echocardiogram confirmation. | 2 |  |
| Low complement        | Decrease in CH50, C3, or C4 below the lower limit of normal for testing laboratory.                                    | 2 |  |
| Increased DNA binding | Increased DNA binding by Farr assay above normal range for testing laboratory.                                         | 2 |  |
| Fever                 | >38°C. Exclude exclude infectious cause.                                                                               | 1 |  |
| Thrombopenia          | <100,000 platelets / x 10  /L, exclude drug causes                                                         | 1 |  |
| Leukopenia            | <3,000 white blood cells / x 10  /L, exclude drug causes                                                   | 1 |  |

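### The SLEDAI-2K form scores proteinuria only when it is new or rising, while Section 7.2.2 scores features that are present; the two rules can give different SRI-4 results for the same patient

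*Protocol*

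**What the plan says.** Section 7.2.2 describes SLEDAI-2K as resting on the presence of 24 characteristics and states: "The features are scored by the evaluating clinician if they were present within the last 30 days". It gives a total "which ranges from 0 to 105".

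The form in Attachment B is headed "Mark, if the descriptor is present at the time of visit or the preceeding 10 days". Its proteinuria item, worth 4 points, reads "New onset or recent increase of more than 0,5mg/24hours". Rash, on the same form, reads "Ongoing inflammatory lupus rash"; alopecia and mucosal ulcers are also worded as ongoing. Haematuria and pyuria are scored on a plain cell count.

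Section 7.3.3 builds SRI-4 on this score. It requires a fall of at least 4 points in SLEDAI-2K, no new BILAG A, at most one new BILAG B, and no worsening of the PGA. It adds that "SRI-4 composite response is the proportion of subjects who achieve a SLEDAI-2K SRI-4 response" at 11 core-study visits and 8 extension visits. Section 9.5.2 names SRI-4 at Week 12 first among the major secondary analyses.

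The only quantitative urine-protein test listed in Section 7.6.3 is "Urinary protein/creatinine ratio" on fresh spot urine. Change in UPCR by visit is a secondary endpoint in its own right (Section 3.2.3).

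**The concern.** The form's proteinuria item depends on newness or increase, whereas Section 7.2.2 depends on presence. A patient whose renal finding has not changed can therefore receive two different totals, depending on which text the assessor follows.

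The size of the item makes this matter, because 4 points is exactly the SRI-4 threshold. Under the form, proteinuria that counted at baseline because it was new stops counting once it is merely stable, and that alone can satisfy the SLEDAI part of the response. In the other direction, proteinuria that was already long-standing at baseline never scores, so its genuine resolution cannot contribute to a response.

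The study is uncontrolled with 10 patients, so no comparison group would share the artefact. Patients with renal findings are foreseen. The nephritis exclusions in Section 5.2 are limited to particular classes and courses, creatinine up to 2.0 mg/dL is allowed in Section 5.1, and UPCR is followed as an endpoint. The same scoring enters the change in SLEDAI-2K by visit.

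**Working it through.** **Inputs.** Item weights and wording come from Attachment B. The scoring rule and range come from Section 7.2.2, the SRI-4 definition from Section 7.3.3, the 10 patients from Section 4.1, and the Week 12 timing (Day 77, ±3 days) from the schedule of events.

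**Step 1: reproduce the plan's own figure.** The form prints 8 items at 8 points, 6 at 4, 7 at 2 and 3 at 1. That is 8 + 6 + 7 + 3 = 24 items and 64 + 24 + 14 + 3 = 105 points, which matches Section 7.2.2. The form is therefore the one the text describes, and the proteinuria item is worth 4 points.

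**Step 2: does the look-back window remove the problem?** No. Proteinuria that began or rose before Day 0 is at least 77 − 3 = 74 days old at Week 12. That is outside both the form's 10 days and the text's 30 days, so it is no longer new or recently increased under either window.

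**Step 3: score two illustrative patients under each rule.** Both have arthritis (4) and raised anti-dsDNA (2) that do not change. Both satisfy the Section 5.1 entry scores under either rule (total at least 6, clinical part at least 4).

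| Patient | Rule | Baseline | Week 12 | Change | SLEDAI part of SRI-4 |
|---|---|---|---|---|---|
| A: proteinuria new at baseline, unchanged at Week 12 | Form | 4 + 4 + 2 = 10 | 4 + 0 + 2 = 6 | −4 | met |
| A | Presence | 4 + 4 + 2 = 10 | 4 + 4 + 2 = 10 | 0 | not met |
| B: long-standing proteinuria, resolved at Week 12 | Form | 4 + 0 + 2 = 6 | 4 + 0 + 2 = 6 | 0 | not met |
| B | Presence | 4 + 4 + 2 = 10 | 4 + 0 + 2 = 6 | −4 | met |

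**Step 4: do the other SRI-4 parts stop patient A?** No. The BILAG and PGA conditions exclude only worsening, and a patient in whom nothing has changed passes both.

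**Step 5: weight of one patient.** 1/10 = 10 percentage points. The exact (Clopper-Pearson) 95% interval is 0 to 30.8% for 0 of 10 and 0.3 to 44.5% for 1 of 10. For mean change in SLEDAI-2K, one such patient shifts the result by 4/10 = 0.4 points.

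**Step 6: the cut-off.** The form prints 0.5 mg per 24 hours. Section 2.1.2 gives its proteinuria target in grams per 24 hours (0.5 to 0.7), and the BILAG form records 24-hour protein in grams. If the gram scale is meant, the printed threshold is 1,000 times too small. No 24-hour collection is scheduled, so the item cannot be read directly from the planned data in either unit.

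**The case against.** The strongest reply is that the protocol body already says features are scored when present. An assessor who follows Section 7.2.2 keeps scoring persisting proteinuria, and no fall from 4 to 0 occurs. This stands as a limit: the documents contain both rules and do not say which governs. It does not remove the point, because the form is what the assessor fills in, and its header asks whether the descriptor is present when the descriptor itself is newness or increase.

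The contrast with the ongoing items also proves little alone. Seizure, cranial nerve disorder and CVA carry onset wording on the same form. The case therefore rests on the conflict with Section 7.2.2.

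A false response needs several things together: proteinuria new or rising just before Day 0, essentially unchanged at Week 12, the form applied over the text, and no new item offsetting the loss. Entry rules make this less likely, because they exclude unstable or progressive disease likely to need escalation and require any oral steroid dose to have been stable for 4 weeks. Read literally, a rise of 0.5 mg per 24 hours could also be met by trivial fluctuation, so even the zero at Week 12 is not certain.

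Other measures limit the damage. UPCR change is reported directly, BILAG records renal findings separately, and LLDAS (Section 7.3.2) has its own condition of no renal activity. All of this bears on how often the problem arises and how far it spreads. None of it makes the two scoring rules agree.

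**Conclusion.** Attachment B and Section 7.2.2 set different rules for a 4-point item, and the difference can decide the SLEDAI part of SRI-4 in either direction. This should be fixed, but it concerns secondary endpoints only: the anti-dsDNA primary endpoint and the sample size are unaffected, and LLDAS is partly protected.

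The effect is 10 percentage points of the SRI-4 proportion per misclassified patient. How many patients that is cannot be derived: the protocol gives no figure for proteinuria at baseline, and the number may be zero.

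A reader might infer that any patient with stable proteinuria becomes a responder, or that the SRI-4 rate is inflated by some stated amount such as 20 to 40 points. The documents support neither. Only proteinuria that was new or rising at baseline, scored by the form, produces a false response. Long-standing proteinuria errs the other way, so the net direction of bias is not established. Any overall percentage would need an assumed prevalence that the protocol does not supply.

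The conclusion uses the SLEDAI-2K definition of SRI-4 in Section 7.3.3. Section 3.2.3 names SELENA-SLEDAI instead, for which no form is attached, and that also needs reconciling.

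**What to change.** Amend the proteinuria item in Attachment B so that it is scored whenever proteinuria above a stated cut-off is present within the look-back window, whether new or persisting, in line with Section 7.2.2. In the same edit:

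- state the cut-off and its unit explicitly, resolving the conflict between the printed milligrams and the gram scale used elsewhere;
- tie the item to the spot UPCR taken at the visit, since no 24-hour collection is planned;
- use one look-back window in both places (10 days on the form, 30 days in the text).

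Then re-score this item at all completed visits, baseline included, from the recorded UPCR values.

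The cost is a small change to the form and re-scoring of one item from data already collected. Visits in Weeks 16 to 32 that were held by video under Section 7.1 may have no UPCR, and those should be listed as not re-scorable. Some SRI-4 responses that rest only on this item may be lost, and some may be gained where persistent proteinuria resolves. Patients who improve by 4 points on other items, such as arthritis, are not affected unless the re-scored item offsets that fall.

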## BRITISH ISLES LUPUS ASSESSMENT GROUP (BILAG-2004) INDEX

| BILAG-2004 INDEX                                                                                                                                                                                                                                                    |               |                                                     |                                     |
|----------------------------------------------------------------------------------------------------------------------------------------------------------------------------------------------------------------------------------------------------------------------------|---------------|-----------------------------------------------------|-------------------------------------|
| 
 
• Only record manifestations/items due to SLE disease activity
 
• Assessment refers to manifestations occurring in the last 4 weeks (compared with the previous 4 weeks)
 
• TO BE USED WITH THE GLOSSARY
 
 |               |                                                     |                                     |
| Record: NA                                                                                                                                                                                                                                                                 | Not Available |                                                     |                                     |
| 0                                                                                                                                                                                                                                                                          | Not present   |                                                     |                                     |
| 1                                                                                                                                                                                                                                                                          | Improving     |                                                     |                                     |
| 2                                                                                                                                                                                                                                                                          | Same          |                                                     |                                     |
| 3                                                                                                                                                                                                                                                                          | Worse         |                                                     |                                     |
| 4                                                                                                                                                                                                                                                                          | New           |                                                     |                                     |
| Yes/No OR Value (where indicated)                                                                                                                                                                                                                                          |               |                                                     |                                     |
| *Y/N Confirm this is due to SLE activity (Yes/No)                                                                                                                                                                                                                          |               |                                                     |                                     |
| CONSTITUTIONAL                                                                                                                                                                                                                                                      |               | GASTROINTESTINAL                             |                                     |
| 1. Pyrexia - documented >37.5° C                                                                                                                                                                                                                                           | ( )           | 56. Lupus peritonitis                               | ( )                                 |
| 2. Weight loss - unintentional >5%                                                                                                                                                                                                                                         | ( )           | 57. Abdominal serositis or ascites                  | ( )                                 |
| 3. Lymphadenopathy/splenomegaly                                                                                                                                                                                                                                            | ( )           | 58. Lupus enteritis/colitis                         | ( )                                 |
| 4. Anorexia                                                                                                                                                                                                                                                                | ( )           | 59. Malabsorption                                   | ( )                                 |
| MUCOCUTANEOUS                                                                                                                                                                                                                                                       |               | 60. Protein-losing enteropathy                      | ( )                                 |
| 5. Skin eruption - severe                                                                                                                                                                                                                                                  | ( )           | 61. Intestinal pseudo-obstruction                   | ( )                                 |
| 6. Skin eruption - mild                                                                                                                                                                                                                                                    | ( )           | 62. Lupus hepatitis                                 | ( )                                 |
| 7. Angio-oedema - severe                                                                                                                                                                                                                                                   | ( )           | 63. Acute lupus cholecystitis                       | ( )                                 |
| 8. Angio-oedema - mild                                                                                                                                                                                                                                                     | ( )           | 64. Acute lupus pancreatitis                        | ( )                                 |
| 9. Mucosal ulceration - severe                                                                                                                                                                                                                                             | ( )           | OPHTHALMIC                                   |                                     |
| 10. Mucosal ulceration - mild                                                                                                                                                                                                                                              | ( )           | 65. Orbital inflammation/myositis/proptosis         | ( )                                 |
| 11. Panniculitis/Bullous lupus - severe                                                                                                                                                                                                                                    | ( )           | 66. Keratitis - severe                              | ( )                                 |
| 12. Panniculitis/Bullous lupus - mild                                                                                                                                                                                                                                      | ( )           | 67. Keratitis - mild                                | ( )                                 |
| 13. Major cutaneous vasculitis/thrombosis                                                                                                                                                                                                                                  | ( )           | 68. Anterior uveitis                                | ( )                                 |
| 14. Digital infarcts or nodular vasculitis                                                                                                                                                                                                                                 | ( )           | 69. Posterior uveitis/retinal vasculitis - severe   | ( )                                 |
| 15. Alopecia - severe                                                                                                                                                                                                                                                      | ( )           | 70. Posterior uveitis/retinal vasculitis - mild     | ( )                                 |
| 16. Alopecia - mild                                                                                                                                                                                                                                                        | ( )           | 71. Episcleritis                                    | ( )                                 |
| 17. Periungual erythema/chilblains                                                                                                                                                                                                                                         | ( )           | 72. Scleritis - severe                              | ( )                                 |
| 18. Splinter haemorrhages                                                                                                                                                                                                                                                  | ( )           | 73. Scleritis - mild                                | ( )                                 |
| NEUROPSYCHIATRIC                                                                                                                                                                                                                                                    |               | 74. Retinal/choroidal vaso-occlusive disease        | ( )                                 |
| 19. Aseptic meningitis                                                                                                                                                                                                                                                     | ( )           | 75. Isolated cotton-wool spots (cytoid bodies)      | ( )                                 |
| 20. Cerebral vasculitis                                                                                                                                                                                                                                                    | ( )           | 76. Optic neuritis                                  | ( )                                 |
| 21. Demyelinating syndrome                                                                                                                                                                                                                                                 | ( )           | 77. Anterior ischaemic optic neuropathy             | ( )                                 |
| 22. Myelopathy                                                                                                                                                                                                                                                             | ( )           | RENAL                                        |                                     |
| 23. Acute confusional state                                                                                                                                                                                                                                                | ( )           | 78. Systolic blood pressure (mm Hg)                 | value ( ) Y/N*                      |
| 24. Psychosis                                                                                                                                                                                                                                                              | ( )           | 79. Diastolic blood pressure (mm Hg)                | value ( ) Y/N*                      |
| 25. Acute inflammatory demyelinating polyradiculoneuropathy                                                                                                                                                                                                                | ( )           | 80. Accelerated hypertension                        | Yes/No ( )                          |
| 26. Mononeuropathy (single/multiplex)                                                                                                                                                                                                                                      | ( )           | 81. Urine dipstick protein (+ = 1, ++ = 2, +++ = 3) | ( ) Y/N*                            |
| 27. Cranial neuropathy                                                                                                                                                                                                                                                     | ( )           | 82. Urine albumin-creatinine ratio                  | mg/mg ( ) Y/N*                      |
| 28. Plexopathy                                                                                                                                                                                                                                                             | ( )           | 83. Urine protein-creatinine ratio                  | mg/mg ( ) Y/N*                      |
| 29. Polyneuropathy                                                                                                                                                                                                                                                         | ( )           | 84. 24-hour urine protein (g)                       | value ( ) Y/N*                      |
| 30. Seizure disorder                                                                                                                                                                                                                                                       | ( )           | 85. Nephrotic syndrome                              | Yes/No ( )                          |
| 31. Status epilepticus                                                                                                                                                                                                                                                     | ( )           | 86. Creatinine (plasma/serum)                       | µmol/L ( ) Y/N*                     |
| 32. Cerebrovascular disease (not due to vasculitis)                                                                                                                                                                                                                        | ( )           | 87. GFR (calculated)                                | mL/min/1.73 m  ( ) Y/N* |
| 33. Cognitive dysfunction                                                                                                                                                                                                                                                  | ( )           | 88. Active urinary sediment                         | Yes/No ( )                          |
| 34. Movement disorder                                                                                                                                                                                                                                                      | ( )           | 89. Active nephritis                                | Yes/No ( )                          |
| 35. Autonomic disorder                                                                                                                                                                                                                                                     | ( )           | HAEMATOLOGICAL                               |                                     |
| 36. Cerebellar ataxia (isolated)                                                                                                                                                                                                                                           | ( )           | 90. Haemoglobin (g/dL)                              | value ( ) Y/N*                      |
| 37. Lupus headache - severe unremitting                                                                                                                                                                                                                                    | ( )           | 91. Total white cell count (x 10  /L)   | value ( ) Y/N*                      |
| 38. Headache from IC hypertension                                                                                                                                                                                                                                          | ( )           | 92. Neutrophils (x 10  /L)              | value ( ) Y/N*                      |
| MUSCULOSKELETAL                                                                                                                                                                                                                                                     |               | 93. Lymphocytes (x 10  /L)              | value ( ) Y/N*                      |
| 39. Myositis - severe                                                                                                                                                                                                                                                      | ( )           | 94. Platelets (x 10  /L)                | value ( ) Y/N*                      |
| 40. Myositis - mild                                                                                                                                                                                                                                                        | ( )           | 95. TTP                                             | ( )                                 |
| 41. Arthritis (severe)                                                                                                                                                                                                                                                     | ( )           | 96. Evidence of active haemolysis                   | Yes/No ( )                          |
| 42. Arthritis (moderate)/tendonitis/tenosynovitis                                                                                                                                                                                                                          | ( )           | 97. Coomb's test positive (isolated)                | Yes/No ( )                          |
| 43. Arthritis (mild)/Arthralgia/Myalgia                                                                                                                                                                                                                                    | ( )           |                                                     |                                     |
| 44. Myocarditis - mild                                                                                                                                                                                                                                                     | ( )           |                                                     |                                     |
| 45. Myocarditis/endocarditis + cardiac failure                                                                                                                                                                                                                             | ( )           |                                                     |                                     |
